| Objectives                                                   | 197-208         | 
 
1) To explore the perceived burden of mental health illnesses associated with cervical cancer diagnosis, or treatment, targeting cervical cancer patients and healthcare workers in the OR Tambo district.
 
2) To assess barriers, practices, and knowledge on cervical cancer screening and HPV vaccination among women and health workers in the Eastern Cape.
 
3) To assess the quality of life of patients with a cervical cancer diagnosis and further determine factors affecting the patient's quality of life.
 
4) To analyse strategies for Health Promoter-Led Mental Wellness Initiatives for early screening and Quality of Life Improvement among Cervical Cancer Patients in the OR Tambo district.
 
5) To conduct a pre-post interventional evaluation of Mental Health Promoter-led early cervical cancer screening and treatment initiation.
 
                                                                                                                                                                                                                                                                                                                                                                                                                                                                                                                                                                                                         | 8     |

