| Intervention and comparator | 252-255 & 440-443      | In the intervention group, four interventions will be implemented at one-month intervals, each followed by an evaluation of quality of life and mental health status outcomes. The four evaluations in the intervention group will run concurrently with those in the control group. The intervention will be implemented by trained Health promoters utilising the Motivational Interviewing Training New Trainers Manual, along with a pocket guide for motivational interviewing and a participant's manual on substance abuse, during the intervention.                                                                                                                                                                           | 10,19  |
|                             | N/A                    | Criteria for discontinuing or modifying allocated intervention/comparator for a trial participant (e.g., drug dose change in response to harms, participant request, or improving/worsening disease)                                                                                                                                                                                                                                                                                                                                                                                                                                                                                                                                  | N/A    |
|                             | 447-551                | To enhance adherence to the mental wellness intervention, participants will receive regular SMS and phone call reminders before each health promoter-led session to support adherence. Attendance will be tracked, with follow-ups conducted within a week for those who miss sessions. Health promoters will offer motivational counselling and brief check-ins, while session logs will record engagement and barriers to ensure the intervention is delivered as intended.                                                                                                                                                                                                                                                         | 19     |

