|                                             |         | will be monitored through emotional check-ins, supervision meetings, and participant reports. All concerns will be documented, reviewed, and addressed following ethical guidelines for participant safety.                                                                                                                                                                                                                                                                                                                                                                                                                                        |       |
| Participant timeline                        | 252-255 | In the intervention group, four interventions will be implemented at one-month intervals, each followed by an evaluation of quality of life and mental health status outcomes. The four evaluations in the intervention group will run concurrently with those in the control group.                                                                                                                                                                                                                                                                                                                                                               | 10    |
| Sample size                                 | 286-299 | $n = \frac{(\sigma_1^2 + \sigma_2^2)(Z_{1-\alpha} + Z_{1-\beta})^2}{(\mu_1 - \mu_2)^2}$ 
The sample size was calculated using the equation, for a two-sided 95% confidence interval, where <math>\alpha = 0.05</math>, <math>Z_{1-\alpha} = 1.96</math>, and for 80% power, <math>Z_{1-\beta} = 0.84</math>. The mean difference <math>\mu_1 - \mu_2 = 1</math> and the standard deviation (<math>\sigma</math>) = 2. The sample size was calculated using a two-sample means formula, assuming a mean difference of 1 and a standard deviation of 2, which corresponds to a medium standardized effect size (Cohen's <math>d = 0.5</math>).
 | 12-13 |

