| Statistical methods                                       | 478-497               | The study will employ descriptive analyses of intervention participants' responses, utilizing means, standard deviations, medians, and interquartile ranges, as appropriate, based on the distribution's normality. Outcome measures of participants in the intervention group will be compared with those in the control group using an appropriate t-test, chi-squared test, Wilcoxon sum-ranked test, and/or the Fisher's exact test, depending on the normality of the distribution, and or the value of the expected frequencies. The study will compare pre- and post-interview guide summative scores using the paired t-test or the Wilcoxon signed-rank tests to ascertain patients' mental health status and quality of life (comparing post-test with pre-test scores) and whether mental health status and quality of life have changed after four months (comparing follow-up post-test with pre-test scores). Univariable and multivariable analyses will also be undertaken using logistic regression to determine the effectiveness of health promoters on the primary outcome measures and factors that are associated with mental health risk among cervical cancer survivors. The risk ratio (RR) will | 20-21 |

|                            |                           |                                                                                                                                                                                                                                                                                                                                                                                                                                                                                                                                                                                                                                                                                                                                                                                                                                                                                                                                                                                                                                                                          |              |

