|----------------------------|---------------------------|--------------------------------------------------------------------------------------------------------------------------------------------------------------------------------------------------------------------------------------------------------------------------------------------------------------------------------------------------------------------------------------------------------------------------------------------------------------------------------------------------------------------------------------------------------------------------------------------------------------------------------------------------------------------------------------------------------------------------------------------------------------------------------------------------------------------------------------------------------------------------------------------------------------------------------------------------------------------------------------------------------------------------------------------------------------------------|--------------|
|                            |                           | be the relative measure of association used. The 95% confidence interval (95% CI) will be used to assess the precision of estimates at the 5% level of significance ( $p \leq 0.05$ ).                                                                                                                                                                                                                                                                                                                                                                                                                                                                                                                                                                                                                                                                                                                                                                                                                                                                                   |              |

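### Change in the primary scores is tested pre-post without the control group, and the arms are compared without adjusting for the baseline scores already collected

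*Protocol*

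**What the plan says.** The Statistical methods row of the protocol's SPIRIT checklist, repeated in the Protocol and statistical analysis plan row, lists three inferential analyses.

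- **Between arms.** "Outcome measures of participants in the intervention group will be compared with those in the control group using an appropriate t-test, chi-squared test", or a rank-sum or Fisher test. The choice depends on the shape of the distribution or on expected cell counts. No baseline term is mentioned.
- **Over time.** A paired t-test or signed-rank test of later against earlier scores, to establish "whether mental health status and quality of life have changed after four months (comparing follow-up post-test with pre-test scores"). The control group does not enter this contrast. The text does not say whether the tests are run per arm or pooled.
- **Model.** Univariable and multivariable logistic regression, which is given the effectiveness question and also a search for factors linked to mental health risk. Its covariates are not named.

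The Outcomes row makes quality of life and the GAD-7 and PHQ-9 scores primary. The Data management row says baseline data are captured, and the Blinding section says allocation is disclosed only once baseline is complete. The Intervention and comparator row says "four interventions will be implemented at one-month intervals, each followed by an evaluation of quality of life and mental health status outcomes", with control evaluations running in parallel.

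**The concern.** A paired test of post against pre answers whether scores moved. It does not say why. Time since diagnosis, recovery from treatment and regression to the mean all move such scores, and they act in both arms. With no single between-arm estimate declared decisive, a significant pre-post change in the intervention group could be reported as if it were an effect.

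The second issue is precision. A baseline measured before allocation is known, on the same scale as the outcome, is usually the most useful covariate a trial of this kind has. The stated between-arm test leaves it out and is more exposed to chance baseline imbalance. The logistic regression does not make this good: it requires the scores to be dichotomised, and nothing says baseline would be a covariate.

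**Working it through.** **Inputs from the protocol.** Significance is judged "at the 5% level of significance". The Sample size row works "for a two-sided 95% confidence interval" (Z = 1.96) "and for 80% power" (Z = 0.84), "assuming a mean difference of 1 and a standard deviation of 2", so d = 1/2 = 0.5. The Allocation concealment row gives 64 per arm.

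**Inputs assumed.** The protocol gives neither the correlation r between baseline and follow-up nor the improvement expected without treatment, so both are shown as ranges.

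**Step 1: the plan's own figure.** n per arm = (2² + 2²)(1.96 + 0.84)²/1² = 8 × 7.84 = 62.72, so 63. The exact t-test calculation gives 63.8, so 64. Power of a two-sample t-test at 64 per arm is 80.1%. The stated size reproduces, and it is sized for the unadjusted test.

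**Step 2: power with baseline adjustment.** ANCOVA reduces the residual SD to 2√(1 − r²), so the effective standardised difference is 0.5/√(1 − r²). Two-sample t power at 64 per arm, two-sided 5%:

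| Assumed r | Variance removed (r²) | Effective d | Power |
|---|---|---|---|
| none (unadjusted) | 0% | 0.500 | 80% |
| 0.3 | 9% | 0.524 | 84% |
| 0.4 | 16% | 0.546 | 86% |
| 0.5 | 25% | 0.577 | 90% |
| 0.6 | 36% | 0.625 | 94% |
| 0.7 | 49% | 0.700 | 98% |

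**Step 3: what a paired test shows when treatment does nothing.** Suppose both arms improve equally, the true difference is zero, and the paired test is run separately in each arm of 64. Let dz be the mean change divided by the SD of change. The probability p that one arm's test is significant is the power of a one-sample t-test with noncentrality dz × √64 = 8 × dz. The arms are independent, so the intervention arm alone is significant with probability p(1 − p).

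| Assumed dz | Intervention arm significant (p) | Intervention arm only, p(1 − p) |
|---|---|---|
| 0.10 | 12% | 11% |
| 0.15 | 22% | 17% |
| 0.25 | 50% | 25% |
| 0.30 | 66% | 23% |
| 0.40 | 88% | 10% |
| 0.50 | 98% | 2% |

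The 25% is a maximum, because p(1 − p) peaks at p = 0.5. As the shared improvement grows, the split result becomes rare, but the intervention arm's own test is then significant almost always. A valid between-arm test stays at 5% throughout.

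**The case against.** A reader might infer that the protocol makes the paired tests its effectiveness analysis. It does not. It plans a comparison with controls and attaches effectiveness to the logistic regression. Nothing says that significance in one arm but not the other counts as an effect, or even that the paired tests are run per arm. The third step therefore shows what such a reading would cost, not an error rate of the stated plan.

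Objective 5, "To conduct a pre-post interventional evaluation", might also be cited as proof of a pre-post design for these outcomes. The objective continues to cervical cancer screening and treatment initiation and does not mention the scores.

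Nor is the between-arm test wrong. Under individual randomisation it is valid, and the sample size matches it. The gain from adjustment depends on correlations that the protocol does not report. The term outcome measures might also cover change scores. That would use baseline, but less well: the SD of change is 2√(2(1 − r)), and normal-approximation power at 64 per arm is 67% at r = 0.3 and 81% at r = 0.5, against 84% and 90% for ANCOVA on the same approximation.

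Finally, covariate lists and the handling of repeated measures are often left to an analysis plan, which is not at hand. Their absence alone would be no finding. What remains is what the protocol does state: an unadjusted, normality-selected test between arms, a control-free test for change, and a model type that does not fit continuous scores.

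**Conclusion.** The point holds as a weakness in the stated analysis that should be fixed, not as a flaw that invalidates the trial. For the continuous primary scores, the protocol names no between-arm analysis that uses baseline. At the planned size and effect, that leaves power at 80% where about 84% to 98% is available for assumed correlations of 0.3 to 0.7.

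The paired tests cannot support a claim of effectiveness. Run per arm with no treatment effect, the intervention arm's test would be significant in about 12% to 98% of trials, and that arm alone in about 2% to 25%, for assumed paired effects of 0.1 to 0.5.

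The validity of the unadjusted test depends on individual randomisation. The Sequence generation section also describes randomising by hospital. If that applied, baseline differences between arms would be likely and ignoring them could also bias the comparison. That contradiction is a separate matter, and baseline adjustment would not resolve it.

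**What to change.** In the Statistical methods row and the identical text in the Protocol and statistical analysis plan row:

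- For each continuous primary score, make the effectiveness analysis a between-arm ANCOVA of the score at the fourth evaluation, adjusted for its baseline value. Report the adjusted mean difference with its 95% confidence interval.
- Drop the normality-based choice of test for these scores.
- Label the paired pre-post tests descriptive, with no claim of effectiveness.

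Two extensions are conditional:

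- Add hospital as a covariate only if randomisation is individual within hospital. If whole hospitals are randomised, arm and hospital coincide and the term cannot be estimated.
- Use a repeated-measures mixed model only if controls are assessed at all four evaluations. The Intervention and comparator row describes parallel evaluations, but it also describes controls being revisited at the end of the intervention period. The two statements must be reconciled first.

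The cost is a rewording before analysis, since ANCOVA needs only baseline and final scores. It brings a linear-model assumption for scores that may be skewed, which robust or bootstrap standard errors can address.

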| Recruitment                                 | 305-310 | Participant recruitment will take place in collaboration with healthcare workers from the oncology units at Nelson Mandela Academic Hospital and St. Elizabeth Hospital. To raise awareness about the study and its benefits, informational sessions will be conducted within the hospitals, accompanied by posters displayed in key areas, such as the women's health units. Health promoters will actively engage potential participants, providing explanations about the study in local languages and assisting with the informed consent process.                                                                                             | 13    |
| Methods: Assignment of interventions |         |                                                                                                                                                                                                                                                                                                                                                                                                                                                                                                                                                                                                                                                    |       |
| Randomization:                              | 236-238 | A randomised control trial of 128 participants with a cervical cancer diagnosis from two hospitals (Nelson Mandela Academic and St Elizabeth hospitals) will be recruited for the intervention.                                                                                                                                                                                                                                                                                                                                                                                                                                                    | 9     |

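### The only analysis tied to four months is a paired pre-post test without a control contrast; the between-arm comparison has no time point and no baseline adjustment

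*Protocol*

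**What the plan says.** The document is a completed SPIRIT 2025 checklist. The analysis text appears twice in the same words, in the rows Protocol and statistical analysis plan and Statistical methods. It sets out, in order:

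- Descriptive summaries: "The study will employ descriptive analyses of intervention participants".
- A comparison of outcome measures between intervention and control by t-test, chi-squared, Wilcoxon or Fisher's exact test. No time point is given.
- Paired t-tests or signed-rank tests of post-test against pre-test, and of follow-up post-test against pre-test. The second is to show "whether mental health status and quality of life have changed after four months (comparing follow-up post-test with pre-test scores". The arm or arms that enter these tests are not stated.
- Univariable and multivariable logistic regression, named as the analysis of the health promoters' effectiveness. No time point is given.

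On design, the Randomization row describes "A randomised control trial of 128 participants with a cervical cancer diagnosis from two hospitals", and the Allocation concealment mechanism row gives 64 per group. The Outcomes row has quality of life, GAD-7 and PHQ-9 assessed in both groups. The Intervention and comparator and Participant timeline rows schedule four evaluations, with those of the control group held at the same times. The Sample size row states: "The sample size was calculated using a two-sample means formula, assuming a mean difference of 1 and a standard deviation of 2". Objective 5 reads: "To conduct a pre-post interventional evaluation of Mental Health Promoter-led early cervical cancer screening and treatment initiation".

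**The concern.** A randomised trial with a concurrent control estimates its effect by comparing the arms at a stated time. Here the one question with a stated time is assigned to a test that leaves the comparison out. A paired test asks whether scores moved. In patients under treatment for cervical cancer, scores may move because of usual care, the course after diagnosis, or regression to the mean. The paired test cannot tell these from the programme, whether it is run in the intervention arm, in each arm separately, or in all 128 together. Nor does a significant result in one arm and a non-significant one in the other test the difference between arms.

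The between-arm comparison that could answer the question is left open. With four evaluations and no time point, a team following the text could report a significant four-month change with no matching between-arm estimate. Objective 5, with its pre-post wording, points the reader the same way.

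**Working it through.** **Inputs from the protocol.** Mean difference 1 and SD 2; "for a two-sided 95% confidence interval" (Z = 1.96); "and for 80% power" (Z = 0.84); 64 per arm.

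**Assumed, not in the documents.** A change of 0.25, 0.5 or 1 point that occurs equally in both arms without any intervention effect; a pre-post correlation r of 0.3, 0.5 or 0.7; no dropout.

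**1. The plan's own figure.** n per arm = (2² + 2²)(1.96 + 0.84)² / 1² = 8 × 7.84 = 62.7, so 63. With the t distribution it is 63.8, so 64. Power with 64 per arm is 80.7% by the normal approximation and 80.1% by t. The stated size reproduces, and it is a size for a between-arm comparison.

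**2. Paired test when the intervention does nothing.** SD of change = 2√(2(1 − r)), which is 2.37, 2.00 and 1.55 for r = 0.3, 0.5 and 0.7. Noncentrality = shift / (SD of change / √64). For a shift of 0.5 and r = 0.5 this is 0.5 / (2/8) = 2.0. The non-central t distribution gives the probability of p < 0.05 in 64 patients:

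| Common shift (points) | r = 0.3 | r = 0.5 | r = 0.7 |
|---|---|---|---|
| 0.25 | 13% | 17% | 25% |
| 0.5 | 38% | 50% | 72% |
| 1 | 91% | 98% | 99.9% |

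If both arms are pooled (n = 128), the ranges are 22-44%, 66-95% and above 99%.

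**3. Between-arm test under the same conditions.** In 20,000 simulated trials with r = 0.5, the between-arm t-test, on final scores or on change, was significant in 5.0% of trials for a shift of 0.5 and in 4.8-4.9% for a shift of 1. Patients were taken as independent.

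**4. Power of the proposed analysis.** With adjustment for the pre-test score, the residual SD is 2√(1 − r²), which is 1.91, 1.73 and 1.43. The standard error of the difference is that SD × √(2/64). For a true difference of 1 and r = 0.5: 1.73 × 0.1768 = 0.306; 1/0.306 = 3.27; 3.27 − 1.96 = 1.31; power about 90%. For r = 0.3 and 0.7 it is about 84% and 98%.

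**The case against.** A reader might infer that the trial wastes its randomisation, and that improvement which would have happened anyway will be reported as the health promoters' effect. The protocol does not support that reading:

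- The sentence just before the paired tests compares intervention with control, the primary outcomes are assessed in both groups, and the sample size is for two independent means.
- Effectiveness is assigned to the logistic regression. The paired tests are said only to show whether scores changed.
- Nothing calls four months the main time point. Controls are revisited at the end of the intervention period, so the between-arm comparison can be read as covering about four months.
- Objective 5 is worded around screening and treatment initiation, and a pre-post evaluation does not exclude a control group.
- The percentages for the paired test are its power to detect a change that is real by assumption. They become false claims of efficacy only if someone makes that claim. No document gives the shifts.
- A time point and baseline adjustment are often left to a statistical analysis plan, which is not shown here.

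Most of this stands, and it limits the point. The last item does not remove it: on the four-month question the protocol is not silent but names a test, and the named test has no control contrast. The between-arm sentence lists only unadjusted tests and does not say which of four evaluations it uses. The logistic regression does not fill the gap either. It also has no time point, and it needs a dichotomised outcome, whereas the trial was sized on a difference in means.

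**Conclusion.** The point holds in a limited form. The protocol answers its one four-month question with an uncontrolled test, and leaves the controlled comparison without a time point or pre-test adjustment. If the paired result were taken as evidence of effectiveness, an ineffective programme would appear to work in about 13-25% of trials for a common shift of 0.25 points, 38-72% for 0.5 and 91-100% for 1. The plan's nominal error rate is 5%. These figures rest on SD 2 from the protocol and on assumed shifts and correlations. The protocol does not say the result will be used that way, although the wording of objective 5 invites it.

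The 5% error rate and the power figures for the between-arm analysis assume individual randomisation. The Sequence generation row also describes randomisation by hospital, with two hospitals. If that applied, the arm contrast would be confounded with hospital and these figures would not hold. That contradiction has to be reconciled separately.

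**What to change.** In both rows that carry the analysis text:

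1. State that the four-month effect on each primary outcome score is the between-arm difference at the four-month evaluation, adjusted for the pre-test score (ANCOVA), with a 95% CI. Say which of the four evaluations is the four-month one.
2. Report paired within-arm change for both arms as description only, not as evidence of effectiveness. Write the descriptive summaries for both arms.
3. Align the wording of objective 5 with the randomised comparison.

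The cost is wording, submitted as a protocol amendment. No new data are needed, because both arms are already measured before and after. The sample size stays at 64 per arm. Under individual randomisation, power is 80-81% unadjusted and about 84%, 90% or 98% with adjustment at assumed correlations of 0.3, 0.5 or 0.7. Like the paired test, a complete-case adjusted analysis uses only patients with both scores, so this change does not address missing data.
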